#### Control group

One hundred milligrams of iron sucrose injection dissolved in 100 mL 0.9% sodium chloride solution will be intravenously administered at the end of dialysis once every 2 weeks for 24 weeks. During this period, participants will continue to receive intravenous biosimilar epoetin treatment in the same way as the experimental group. For the first intravenous infusion of iron sucrose injection, a small test dose will be performed. The test method refers to the drug instructions of iron sucrose injection, which are as follows.
Dosage: 1–2.5 mL (20–50 mg iron content) for adults. Children should be given 1 mL (iron content 20 mg) each time with body weight > 14 kg and given half of the daily dose (body weight kg × 1.5 mg/kg) each time with body weight < 14 kgCaution: cardiopulmonary resuscitation equipment should be available during the test. If no adverse reactions occur after 15 min of administration, the remaining administration can be continued

### Dose adjustment within the next 24 weeks

If TSAT < 20% occurs during the test, the dosage of the iron agent will be adjusted as follows.
Iron polysaccharide complex: The iron polysaccharide complex prescription will be adjusted from one capsule daily to two capsules twice dailyIron sucrose injection: the prescription of iron sucrose injection will be adjusted from “100 mg/time, intravenous drop, once every two weeks” to “100 mg/time, once a week.” If SF ≥ 500 μg/L and/or TSAT ≥ 50% after the above treatment, iron supplementation therapy will be stopped and SF and TSAT will be reevaluated twice a week. If SF < 200 μg/L and/or TSAT < 20%, or SF 200–500 mg/L and/or TSAT 20%–50% are found twice consecutively, iron supplementation therapy will be restarted. Iron supplementation therapy is iron sucrose injection 100 mg/time, intravenous drip, once a week

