**Methods:**

This randomized controlled trial uses an open-label, parallel group design, where the efficacy and safety of maintenance hemodialysis (MHD) participants is evaluated. The experimental group is assigned erythropoietins and iron polysaccharide complex (two capsules each time, bid), and the control group is assigned erythropoietin and sucrose iron (100mg, 2w) injection. Participants (aged 18–75 years) undergoing maintenance hemodialysis were considered for screening. Inclusion criteria included hemoglobin (Hb) ≥110g/L and < 130g/L, transferrin saturation (TSAT) > 20% and < 50%, and serum ferritin (SF) > 200μg/L and < 500μg/L. Exclusion criteria included acute or chronic bleeding, serum albumin < 35g/L, hypersensitive C-reactive protein (HsCRP) > 10 mg/L, and severe secondary hyperparathyroidism (iPTH ≥ 800 pg/mL). Full inclusion and exclusion criteria are described in the “Methods” section. The primary endpoint is TSAT of the participants at week 12. Secondary endpoints include Hb, SF, hematocrit (Hct), HsCRP, pharmacoeconomic evaluation, drug costs, quality of life, and indicators of oxidative stress. The treatment will last for 24 weeks with a follow-up visit at baseline (within 7 days prior to initial treatment) and weeks 4, 8, 12, 16, 20, and 24 after initial treatment. This clinical research includes 9 hemodialysis centers in mainland China and plans to enroll 186 participants.

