### Trial design

This study is a multicenter, parallel controlled, randomized, open clinical trial (version 1.1; date 11 Dec. 2019, phase IV post-marketing) in China, which has been registered with the Chinese Clinical Trial Registry (http://www.chictr.org.cn/index.aspx) on March 23, 2020. The trial registration number is ChiCTR2000031166. The detailed flowchart is shown in Fig. 1. All eligible participants will be randomly divided into two groups in a 1:1 ratio: experimental group [conventional drug (erythropoietin) therapy+ iron polysaccharide complex] and control group [conventional drug (erythropoietin) therapy + iron sucrose injection]. Participants will complete the study visit at baseline (within 7 days before the first treatment) and weeks 4, 8, 12, 16, 20, and 24 after the first treatment. We used the SPIRIT reporting guidelines [11] in the current study.

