### Intervention

#### Experimental group

Iron polysaccharide complex (150mg) will be taken orally, 2 capsules per day, for 24 weeks. Participants will be treated with biosimilar epoetin (no need to dilute) intravenously with a single dose of 10,000U once a week during the maintenance period. At the same time, biosimilar epoetin dosage will be adjusted according to the measured hemoglobin concentration, as follows [7].
Discontinue biosimilar epoetin if Hb ≥ 130 g/L. Hb levels will be checked once every 2 weeks. If the Hb level drops to 110–130 g/L, the original biosimilar epoetin dose will be reduced by 25% or extended to once in 10 days for continuation.If Hb < 110 g/L, TSAT, and SF are met, biosimilar epoetin will be administered as a single dose of 10,000U at least three times, every 2 weeks. Also, the Hb values of participants will be evaluated once every 2 weeks. The maximum dose of biosimilar epoetin will be 10,000U twice a week. If TSAT and SF fail to meet the standard, the iron deficiency will be corrected first, and the biosimilar epoetin treatment regimen will be adjusted once TSAT and SF are within the desired range.

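### Iron is stepped up on TSAT alone although low ferritin alone can lead to exit, and the oral step-up starts from a dose assigned nowhere

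*Protocol article*

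**What the plan says.** All references are to the protocol article.

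- **Step-up** (*Dose adjustment within the next 24 weeks*): the trigger names TSAT only, in the words "If TSAT < 20% occurs during the test, the dosage of the iron agent will be adjusted as follows". The oral prescription goes from one capsule a day to two capsules twice a day. Iron sucrose goes from 100 mg every two weeks to 100 mg every week.
- **Stop and restart** (same section): iron stops at SF ≥ 500 μg/L and/or TSAT ≥ 50%. Restart begins with "If SF < 200 μg/L and/or TSAT < 20" per cent, but iron also restarts when SF of 200–500 and/or TSAT of 20–50% is found twice in a row.
- **Entry** (*Inclusion criteria*): SF above 200 and below 500 μg/L, TSAT above 20% and below 50%, haemoglobin (Hb) at least 110 and below 130 g/L.
- **Exit** (*Withdrawal and drop-out*): SF ≤ 200 μg/L or TSAT ≤ 20% over two consecutive months. Either one is enough.
- **Epoetin rule at low Hb** (*Experimental group*): "If Hb < 110 g/L, TSAT, and SF are met, biosimilar epoetin will be administered as a single dose of 10,000U"; otherwise, "If TSAT and SF fail to meet the standard, the iron deficiency will be corrected first". The control arm follows the same rule: "participants will continue to receive intravenous biosimilar epoetin treatment in the same way as the experimental group".
- **Assigned oral dose**: *Experimental group* has "Iron polysaccharide complex (150mg) will be taken orally, 2 capsules per day, for 24 weeks", while the abstract's Methods has "iron polysaccharide complex (two capsules each time, bid".

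**The concern.** A titration rule normally gives the participant a dose response before a withdrawal rule removes them. Here low ferritin counts towards withdrawal but triggers no dose step in someone still taking iron. Entry permits SF just above 200 μg/L, so a small fall is enough to reach this state, and Hb need not fall at all. Withdrawals of this kind would reduce retention and could cost 24-week secondary outcomes.

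The second problem exists whatever the trigger. The oral step-up is written from a starting dose that neither statement of the regimen assigns. Under one of those statements it produces no increase, while the comparator's dose doubles on the same trigger.

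**Working it through.** **1. The rules side by side, for a participant currently on iron**

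| TSAT | SF (μg/L) | Hb (g/L) | Step-up (TSAT < 20%) | Stop (SF ≥ 500 or TSAT ≥ 50%) | Counts towards exit (SF ≤ 200 or TSAT ≤ 20%) | Other iron instruction |
|---|---|---|---|---|---|---|
| 18% | 300 | 115 | yes | no | yes | none |
| 25% | 300 | 115 | no | no | no | none |
| 25% | 150 | 115 | **no** | no | **yes** | none |
| 45% | 150 | 115 | **no** | no | **yes** | none |
| 25% | 150 | 100 | **no** | no | **yes** | correct deficiency first, no dose |

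The restart rule cannot fill rows 3 to 5, because it applies only after iron has been stopped. In rows 3 and 4 exit is the only stated consequence of low SF, and maintenance iron simply continues. In row 5 correction is ordered without dose, agent or frequency, and the wording leaves open whether low SF with adequate TSAT fails the standard.

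**2. Size of the step-up**

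- Intravenous: 100 mg / 2 weeks = 50 mg/week, raised to 100 mg/week; 100 / 50 = ×2.
- Oral target: 2 capsules × 2 = 4 capsules/day.
  - From 1/day (the step-up text): 4 / 1 = ×4.
  - From 2/day (*Experimental group*): 4 / 2 = ×2.
  - From 2 × 2 = 4/day (abstract): 4 / 4 = ×1, no increase.

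**3. When exit could occur**

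*Trial design* places visits at "weeks 4, 8, 12, 16, 20, and 24 after the first treatment". If SF is checked at each visit (an assumption, since Fig. 2 is not shown), SF low from week 4 meets the rule at week 8 if two consecutive monthly values suffice, or at week 12 if a full eight weeks is meant. If SF is measured only at weeks 0, 12 and 24, the times listed under *Secondary endpoints*, two low monthly values cannot occur before week 12.

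**4. Retention**

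The stated requirement of 154 reproduces closely. Reading the 11% as a standard deviation, 2 × (1.960 + 0.842)² × 11² / (7 − 2)² = 76.0 per arm, or 152 in all. Against the stated 154, planned enrolment leaves 186 − 154 = 32 participants (32 / 186 = 17.2%) for losses of every kind. The article gives nothing from which the share of those losses due to low SF could be estimated.

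**The case against.** Titrating on TSAT alone is a coherent choice. The population has corrected anaemia, the background stresses iron overload and oxidative stress, and holding the dose at adequate TSAT is defensible. Titration and withdrawal rules serve different purposes and need not share triggers; both can be followed as written. This stands as a reason not to insist on extra iron. It does not explain why participants should leave for a value the protocol has chosen not to treat.

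Several stronger readings are tempting but not supported:

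- *That the restart rule shows 200 μg/L to be an action threshold.* Iron also restarts at SF 200–500 found twice, so it resumes on either side of 200. The inconsistency rests on the step-up and exit rules, with entry as context.
- *That nothing is said about iron at low SF.* At Hb below 110 g/L correction is ordered in both arms. Only the dose is missing there, and the full protocol, which is not shown, may give it.
- *That participants will be lost before the week-12 primary measurement.* This depends on an SF schedule that is not shown.
- *That the primary comparison is biased.* Nothing in the article shows that the arms would be affected differently by the SF rule. Withdrawing participants must have a final evaluation, and the intention-to-treat set excludes nobody after randomization. A final evaluation before week 12 is not the week-12 TSAT, but that is a limit on the mitigation and not evidence of bias.

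The difference between < 20% for step-up and ≤ 20% for exit affects only values exactly at the limit and carries no weight. The capsule conflict is a separate defect and should not be used to enlarge the ferritin point.

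**Conclusion.** Two points hold on the text. First, at Hb of 110 g/L or more with TSAT from 20% to below 50%, a participant on iron with low SF has no stated iron response before the exit criterion is met; below 110 g/L there is an instruction without a dose. Second, the oral step-up is wrong as written: its starting dose is assigned nowhere, and the real increase is a doubling or nothing, depending on which statement of the regimen governs.

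Condensation into an article does not account for either, since the triggers, limits and doses involved are all stated explicitly. Severity is minor to moderate. How many participants would be affected, and whether the primary result would change at all, cannot be computed from the document.

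**What to change.** 1. **Oral dose.** Settle the assigned dose and write the step-up from it. With two capsules a day, step to two capsules twice daily, a doubling that matches the control arm. If the assigned dose is already two capsules twice daily, name a different step.
2. **Ferritin rules.** Choose one:
   - (a) trigger the arm-specific step-up on TSAT < 20% or SF < 200 μg/L, unless the stop rule applies; or
   - (b) if titration on TSAT alone is intended, say so and remove SF alone from the exit criteria.
3. **Reporting.** Report step-ups by arm and by trigger.

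**Cost.** A short amendment to the dose-adjustment text, the dose statements and, under (b), the exit criteria, with no added visits or tests. Option (a) gives some participants in both arms more iron despite adequate TSAT, with an unknown, probably small, effect on week-12 TSAT. For a step-up at week 4 the most this adds is:

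- Control arm: 50 mg/week × 8 = 400 mg by week 12, and 50 × 20 = 1,000 mg by week 24.
- Oral arm, from two capsules a day: 2 × 56 = 112 capsules by week 12, and 2 × 140 = 280 by week 24 (2 × 150 = 300 mg/day more if 150 mg is the content of one capsule).

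Option (b) adds no iron, but participants with low SF stay on an unchanged dose while TSAT remains in range.

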Iron supplementation is an important management strategy for CKD-related anemia. The 2020 edition of Chinese Medical Doctor Association guidelines recommends that hemoglobin levels and iron metabolism status should be identified first and addressed with potential causes of iron deficiency, before starting iron therapy [7]. Whether or not they are treated with recombinant human erythropoietin (EPO), patients with absolute iron deficiency should be treated with iron supplements. Also, patients with functional iron deficiency should be treated with iron supplements after weighing the benefits and risks of treatment. Commonly used iron agents are intravenous iron and oral iron. However, iron overload still exists in clinical intravenous iron therapy. Iron overload further causes increased levels of oxygen free radicals and increased oxidative stress. In 2011, the Japanese Society for Dialysis first warned about the potential toxicity of intravenous iron maintenance therapy [8]. The issue of iron overload continues to be addressed in several guidelines around the world [9]. Moreover, oxidative stress caused by intravenous iron is also a concern for nephrologists. Oral iron reduces the risk of iron overload and has little effect on oxidative stress, but the first and second generations of oral iron have obvious gastrointestinal side effects. Polysaccharide iron complex capsule is the third generation of oral iron agent that has been widely used in clinical practice due to its advantages of little or no stimulation of the gastrointestinal tract, few side effects, stable coordination, good solubility, and high iron content.

Although the PIVOTAL trial [10] has demonstrated the safety of relatively high levels of ferritin and TSAT with IV iron, iron therapy is still a challenge in the clinical treatment of CKD-related anemia; hence, it is necessary to conduct clinical studies to explore the optimal treatment of CKD-related anemia [7–9]. This study is the first multicenter clinical study of iron polysaccharide complex in CKD participants with maintenance hemodialysis. It aims to evaluate the clinical efficacy and safety of oral iron and to provide additional drug options in the treatment of anemia in CKD participants. This study will offer treatment alternatives for people on maintenance dialysis, especially home therapies such as peritoneal dialysis or home hemodialysis, in whom IV iron is inconvenient.

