#### Secondary endpoints

TSAT of participants’ changes between groups at 24 weeks of treatmentHb, SF, Hct, and HsCRP values of participants’ changes between groups at 0, 12, and 24 weeks of treatmentDrug costs for participants’ changes between groups at 24 weeks of treatment (including cumulative biosimilar epoetin dose and iron supplementation)Quality of life scale scores EQ5D-5L of participants’ changes between groups prior to treatment and at 24 weeks of treatment [12]Indicators of oxidative stress, including malondialdehyde (MDA), superoxide dismutase (SOD), and glutathione peroxidase (GSH-Px), will be measured in participants’ changes between groups at 0, 12, and 24 weeks of treatment [12]Cardiovascular events during the follow-up

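### The only upper-limit iron rule names no arm and restarts iron solely as weekly IV iron sucrose, so it either moves participants off their assigned regimen or leaves some with no specified stop

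*Protocol article*

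**What the plan says.** The section Dose adjustment within the next 24 weeks opens with a low-iron trigger: "If TSAT < 20% occurs during the test, the dosage of the iron agent will be adjusted as follows". It then gives one escalation per drug. The oral complex goes up to two capsules twice daily. Iron sucrose goes from 100 mg every two weeks to 100 mg weekly.

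The upper-limit rule follows directly on the iron sucrose escalation. Once either index reaches its ceiling (500 μg/L for SF, 50% for TSAT), the text directs that "after the above treatment, iron supplementation therapy will be stopped and SF and TSAT will be reevaluated twice a week". Iron restarts if SF is below 200 μg/L and/or TSAT is below 20%, or if "SF 200–500 mg/L and/or TSAT 20%–50% are found twice consecutively, iron supplementation therapy will be restarted". The restart regimen is given once, with no arm named: "Iron supplementation therapy is iron sucrose injection 100 mg/time, intravenous drip, once a week".

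The assigned regimens are oral complex for 24 weeks (Experimental group) and iron sucrose 100 mg, which "will be intravenously administered at the end of dialysis once every 2 weeks for 24 weeks" (Control group).

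**The concern.** A stop-and-restart rule should say whom it covers and return each participant to their own treatment. This one does neither clearly, and its single restart regimen is the comparator drug at the escalated rate.

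Two things are at stake.

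- **Safety.** Depending on how a site reads the rule, a participant with high indices is not stopped by rule, or is restarted on IV iron or on a higher dose. The Background gives iron overload as a concern with IV iron ("However, iron overload still exists in clinical intravenous iron therapy") and as a reason for the oral route ("Oral iron reduces the risk of iron overload and has little effect on oxidative stress").
- **Comparison.** If oral-arm participants restart on iron sucrose, or controls restart at a doubled rate, the arms no longer represent the regimens being compared. That could touch week-12 TSAT when a limit is crossed and acted on before week 12. It could also touch the 24-week oxidative-stress and drug-cost comparisons, the latter "including cumulative biosimilar epoetin dose and iron supplementation". Because the protocol itself directs the switch, the per-protocol definition (Data set category) does not clearly remove these participants.

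**Working it through.** The plan gives no figure on this point to reproduce. The check sets the sections side by side and adds simple dose arithmetic.

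**1. Is there another upper-limit rule?** The upper SF and TSAT bounds in Inclusion criteria govern entry. The SF/TSAT item in the Exit criteria covers low values only. The instruction on SF and TSAT under Experimental group concerns deficiency. Only the dose-adjustment section acts on high values during treatment.

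**2. What follows under each scope?**

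| Scope of the rule | Oral arm | Controls on assigned dose | Escalated controls |
|---|---|---|---|
| Everyone | Restart on the comparator | Restart at twice the assigned rate | Same drug, same rate |
| Only those escalated for TSAT < 20% | Unescalated: no specified stop; escalated: restart on the comparator | No specified stop | Same drug, same rate |
| Iron sucrose arm, all controls | No specified stop | Restart at twice the assigned rate | Same drug, same rate |
| Iron sucrose arm, escalated only | No specified stop | No specified stop | Same drug, same rate |

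**3. Rate.** Assigned: 100 mg / 2 weeks = 50 mg/week. Restart: 100 mg/week. Ratio: 100 / 50 = 2.

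**4. Restart trigger.** The printed SF range in mg/L is taken here as μg/L. Read literally, the two alternatives together say: restart if either index is at or below its upper limit on two consecutive readings. There are three ways to be stopped.

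- SF high only: TSAT is already below 50%, so the trigger is met.
- TSAT high only: SF is already below 500 μg/L, so the trigger is met.
- Both high: not met until one falls.

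A participant stopped at SF 600 μg/L with TSAT 35% therefore qualifies on the next two rechecks if neither value changes. With rechecks twice a week, that is about a week later.

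**5. Illustration of iron sucrose given before the week-12 sample.** Assumption: the limit is acted on at the week-4 visit, before that day's dose. Visit weeks are in Trial design. Secondary endpoints lists SF only at weeks 0, 12 and 24, and the schedule figure is not shown.

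- Control never stopped: weeks 0, 2, 4, 6, 8, 10 = 6 × 100 = 600 mg.
- Control stopped at week 4 and restarted weekly from week w: 200 + 100 × (12 − w). For w = 5 this is 900 mg; w = 8, 600 mg; w = 10, 400 mg. With no restart before week 12 it is 200 mg. Against 600 mg the range is +300 to −400 mg.
- Oral-arm participant stopped at week 4, with the rule applied across arms: 100 × (12 − w) of the comparator. For w = 5 this is 700 mg; w = 8, 400 mg; no restart, 0 mg.
- If the first reading acted on is week 12, the effect on the primary endpoint is 0.

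**The case against.** The strongest reply is that the rule is coherent on its narrowest reading. It follows the iron sucrose escalation, applies after that treatment, and restarts the same drug at the same weekly dose. On that reading nobody crosses over and no dose is doubled. The article is also a condensation, and its list layout was flattened in extraction, so the position of the sentence is weak evidence of scope. This stands for escalated controls. It does not rescue the rule, because that reading gives no stop to the oral arm or to controls on the assigned dose. The stop, recheck, trigger and restart drug are all printed, so the problem lies in stated text and not in missing detail.

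Further points against:

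- For a control whose TSAT has fallen below 20%, weekly iron sucrose is what the escalation rule prescribes anyway. This stands: doubling is a defect only for unescalated controls restarted with TSAT at or above 20%.
- The and/or wording may have been meant to refer to whichever index caused the stop. That is possible, but the text does not say so.
- The Background also cites a trial as showing that relatively high ferritin and TSAT with IV iron are safe. In addition, the investigator may withdraw a participant, and a data monitoring committee exists. These temper the safety concern, but they are evidence, discretion and oversight, not a dosing rule.

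A reader might infer that most participants are affected, since most cells of the table show a problem. The cells are categories of unlike problems and say nothing about how many people fall in each.

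**Conclusion.** The point holds and should be fixed. The only upper-limit rule shown has no stated scope, and every plausible scope leaves some participants either without a specified stop or restarted on the comparator or at twice their assigned rate. The literal trigger separately permits restart in two of the three stop patterns while the index that caused the stop is still high.

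The size in participants is unknown, because the article gives no rate of crossing the limits. A reader might go further and infer that the rule biases the week-12 non-inferiority comparison, for instance by making the oral arm look like the comparator. The document does not support that. The share affected is not given, time off iron and later weekly dosing pull total exposure in opposite directions, and the effect may be zero if no limit is acted on before week 12. The milligram range above rests on the assumed week-4 action and shows only that exposure could move either way.

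**What to change.** Rewrite the upper-limit paragraph as a standalone rule:

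1. Stop iron in either arm at any reading with SF ≥ 500 μg/L and/or TSAT ≥ 50%.
2. Restart only when SF is < 500 μg/L and TSAT is < 50% on two consecutive readings.
3. Restart on the participant's own assigned drug, at no more than the dose in use when the limit was crossed. The exception is TSAT < 20%, where the existing arm-specific escalation applies. Without this exception the dose cap would contradict the escalation rule.
4. Correct the unit in the restart range from mg/L to μg/L.

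The assigned oral dose should be settled in the same edit, since the Abstract (two capsules twice daily), Experimental group (two per day) and the escalation text (starting from one daily) differ.

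The cost is a protocol amendment, reported to the ethics committees and sent to the nine sites. If the rule is now being applied narrowly, there will also be some extra twice-weekly SF/TSAT rechecks for participants newly covered by the stop. No extra participants are needed.

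### The iron restart rule can be met while the stop rule still applies, and no arm is named for the stop or the iron sucrose restart

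*Protocol article*

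**What the plan says.** All references are to the protocol article. Under Dose adjustment within the next 24 weeks, the opening rule raises the iron dose in either arm when TSAT falls below 20%. In the text as read from the PDF, the two list items run together: "adjusted from one capsule daily to two capsules twice dailyIron sucrose injection: the prescription of iron sucrose injection will be adjusted". The stop rule follows the iron sucrose item. It applies to SF of at least 500 μg/L and/or "TSAT ≥ 50% after the above treatment, iron supplementation therapy will be stopped". SF and TSAT are then rechecked twice a week.

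Restart has two branches. The low branch is SF below 200 μg/L and/or TSAT below 20%. The in-range branch reads "or SF 200–500 mg/L and/or TSAT 20%–50% are found twice consecutively, iron supplementation therapy will be restarted". The regimen is then given: "Iron supplementation therapy is iron sucrose injection 100 mg/time, intravenous drip, once a week".

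The control arm's assigned iron sucrose is "intravenously administered at the end of dialysis once every 2 weeks for 24 weeks". The oral starting dose is printed in three ways:

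- Abstract, Methods: "iron polysaccharide complex (two capsules each time, bid"
- Experimental group: "will be taken orally, 2 capsules per day, for 24 weeks"
- Dose adjustment section: one capsule daily before escalation

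**The concern.** A stop rule for iron overload should not allow iron again while the index that triggered it is still high. As printed, this one can.

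The block also does not say whom it covers, yet the only product it names for restart is the comparator. The comparison is non-inferiority (Sample size; Discussion), and the main analysis set excludes nobody after randomization (Data set category). Comparator iron given in the oral arm would therefore stay in that arm's results and tend to bring the arms together. Whether the per-protocol set would exclude such participants is not stated. If the block covers controls only, the oral arm lacks a printed stop for high SF or TSAT. Sites could apply the text differently.

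**Working it through.** No figure in the plan depends on this rule, so the check is of logic.

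**Inputs.** Limits are SF 200 and 500 μg/L and TSAT 20% and 50%, from the dose-adjustment section. Test values are SF 150 / 350 / 700 μg/L (low / in range / high) and TSAT 15 / 30 / 55%. That gives 3 × 3 = 9 bands.

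**Stop, either index sufficient.** Three bands have high SF, three have high TSAT and one is counted twice: 3 + 3 − 1 = 5 bands stop and 4 do not.

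**Restart among the 5 stop bands:**

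| Low branch | In-range branch | Also meet restart | Which (SF + TSAT) |
|---|---|---|---|
| OR | OR | 4 | low+high, in+high, high+low, high+in |
| OR | AND | 2 | low+high, high+low |
| AND | OR | 2 | in+high, high+in |
| AND | AND | 0 | none |

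SF 700 with TSAT 30% (high+in) meets both rules in the two readings where the in-range branch is OR. Requiring two consecutive findings does not prevent this, because the same discordant pair can be found twice.

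**Cost of AND/AND.** Of the 4 non-stop bands, low+low and in+in can restart. Low+in and in+low meet neither branch, so 2 of 4 have no restart route.

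**Stop read as AND.** Only high+high stops (1 band) and no band overlaps, but SF 700 with TSAT 30% is then never stopped.

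**Endpoints.** With stop as OR and the printed ranges taken to include their ends, (SF 500, TSAT 30%), (350, 50%) and (500, 50%) meet both rules on all four restart readings. With strict upper limits, as in Inclusion criteria, an in-range branch read as AND no longer fires at these points.

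**Scope.**

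| Stop covers | Sucrose restart covers | Result for the oral arm |
|---|---|---|
| both arms | both arms | restarts on the comparator |
| controls | controls | no printed stop for high SF or TSAT |
| both arms | controls | stopped, with no restart product |

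No other section supplies an oral-arm stop. The adjustment rules under Experimental group concern epoetin, and the iron exit criterion under Withdrawal and drop-out covers low values only. If the block also covers controls who were never escalated, they restart on 100 × 12 = 1,200 mg per 12 weeks, against 100 × 6 = 600 mg as assigned.

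**Timing.** Visits are at "weeks 4, 8, 12, 16, 20, and 24 after the first treatment", but the assessment schedule (Fig. 2) is not shown.

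- If indices are tested at every visit, a stop at week 4 plus two twice-weekly checks gives a restart at about week 5. If escalation must come first, it is about week 9.
- If they are tested only at weeks 12 and 24, the earliest restart is about week 13, after the primary endpoint. If escalation must come first, there is none within treatment.

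**Oral dose.** The three printed starting doses are 4, 2 and 1 capsules per day. Escalating to 4 per day multiplies the dose by 1, 2 or 4, against 2 in the control arm.

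**Proposed rule.** Restart if SF < 500 AND TSAT < 50% is the exact complement of stop if SF ≥ 500 OR TSAT ≥ 50%. It gives 0 conflicts in the 5 stop bands, covers 4 of 4 non-stop bands and is false at each endpoint above.

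**The case against.** The best defence is that the block belongs to the iron sucrose item. It follows the sucrose escalation sentence, refers back to the treatment just described, and restarts at that item's escalated dose. Read so, nobody crosses over and no escalated control's dose doubles. In sequence (stop, recheck, resume), in-range values can also be taken to mean a return to target on both indices, as Inclusion criteria require. The article condenses a fuller protocol, which may be clearer.

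Much of this stands, and it rules out several stronger inferences that a reader might draw:

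- **That oral-arm participants will cross over and bias the trial towards non-inferiority.** This needs the two-arm reading, which the layout does not favour, although the lost list breaks make layout weak evidence. Even then, only those reaching a stop limit could cross over, and perhaps only after escalation for low TSAT. No frequency is given.
- **That the oral arm must either cross over or lack a stop rule.** The third row of the scope table is also possible.
- **That the oral arm has no ceiling on iron.** Two capsules twice daily is the highest printed dose, investigators may withdraw participants, and a data monitoring committee is described. What is missing is a printed stop for high indices.
- **That the endpoints conflict on every reading.** That assumes inclusive limits, and Inclusion criteria uses strict ones.
- **That the mg/L unit causes the overlap.** It is a misprint. SF 700 with TSAT 30% conflicts through TSAT whatever the ferritin unit.

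The defence does not rescue the wording. The both-indices reading sets aside the printed and/or and strands 2 of the 4 non-stop bands, and each scope reading leaves the oral arm a problem. These are treatment instructions as stated, so this is not detail left to another document.

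**Conclusion.** The point holds as a defect in a printed treatment rule that should be fixed. On the plain and/or reading, iron may restart while the triggering index is still high. Reading both restart branches as AND removes that, apart from the shared endpoints as printed, but leaves participants with one low and one in-range index without a restart route. Scope is unstated, with one of three consequences for the oral arm.

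The size is logical only: 4, 2, 2 or 0 of 5 stop bands overlap, according to the restart reading, with stop read as OR. These are bands and not patients, and the ratio depends on how the bands are drawn. The number affected and any effect on week-12 TSAT cannot be computed, and an effect before week 12 requires testing before then. Confidence is high that the wording is defective. The documents do not establish that crossover would occur.

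**What to change.** Replace the block with one rule for all participants in both arms, escalated or not:

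- Stop iron if SF ≥ 500 μg/L OR TSAT ≥ 50%.
- Restart only when SF < 500 μg/L AND TSAT < 50% on two consecutive checks, on the assigned product.
- State the restart dose for each arm. The choice is the sponsor's.
- If intravenous iron in the oral arm is intended, define it as rescue with a named low-iron trigger.
- Correct mg/L to μg/L in the restart band.
- State one oral starting dose consistently in the Abstract, Experimental group and the dose-adjustment section. Two capsules per day would make escalation a doubling, as in the control arm, but this too is the sponsor's choice.

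The cost is low: a few sentences of protocol correction and a notice to the 9 centers. The sample size does not change.
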